##### Qualitative analysis

The audio-recorded interviews of the ENABLE GOI will be coded by study team members ([name]) [40] in Atlas.ti using a qualitative content analysis approach using *a* priori domains from the GOI measure and additional categories that emerge from the inductive review of transcripts [65]. Coded data will be aggregated and reviewed within and across codes to construct an in-depth understanding of facilitators, barriers, and contextual factors that may influence implementation of the ENABLE program.

Findings from the qualitative data will be integrated with the main findings of the RCT at the interpretation and reporting stage [66]. We will use a convergent mixed methods analysis to collect both qualitative and quantitative ENABLE GOI data at roughly the same time, assess information using parallel constructs for both types of data, separately analyze both types of data, and then compare results through discussion and jointly displaying both forms of data. The joint display will map each ENABLE GOI domain score to corresponding concepts or themes from these qualitative findings to more fully understand the context of the GOI domain scores and identify patterns across practice clusters [67]. This will provide validation for each data type and create a foundation for drawing conclusions about the implementation of the ENABLE program [68].

#### Analysis for exploratory aims (patient and caregiver outcomes)

##### Exploratory aim 1

To compare NCORP practices randomized to VLC or TA on patient and caregiver quality of life and mood, linear mixed models will be used to estimate differences in patient and caregiver outcome trajectories over the 24-week follow-up period. If necessary, a false discovery rate adjustment will be used to adjust for multiple exploratory inferences [69].

##### Exploratory aim 2

The association between ENABLE sessions and change in patient outcomes will be examined with linear mixed models. Adjusting covariates will include patient characteristics that may influence participation in sessions (e.g., sex, illness acuity, age). Linear mixed models will also be used to examine the association between GOI scores and patient outcomes.

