### Primary aim (implementation outcome, patient level)

Compare the effectiveness of VLC vs. TA on ENABLE program uptake, as measured by the proportion of patients who complete the ENABLE program (i.e., have a palliative care assessment and complete the six ENABLE sessions). *Hypothesis*: Practice clusters randomized to VLC will have greater ENABLE program uptake than practice clusters randomized to TA.

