### Exploratory aim 1 (patient & caregiver outcomes)

Compare practice clusters randomized to VLC or TA on patient and caregiver quality of life (QOL) and mood outcomes. *Hypothesis*: Patients and caregivers at practice clusters randomized to VLC will have better QOL and mood compared to those at practice clusters randomized to TA.

### Exploratory aim 2

Determine the relationship among ENABLE program uptake, overall ENABLE program implementation, and patients’ QOL and mood across the two strategies. *Hypothesis*: Practice clusters with better ENABLE program uptake and overall ENABLE implementation (regardless of implementation group) will demonstrate a higher degree of improved patient outcomes (i.e., QOL and mood) compared to practice clusters that have low/poor ENABLE program uptake and overall ENABLE implementation.

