### Exploratory aim: patient measures

Table 2 presents patient measures. Patient assessments will be completed at baseline, 12, and 24 weeks. There will be several options to collect the data: [1] study coordinator reads the questions to the patient (either in person or on the phone) and enters the patient responses, [2] the patient completes the assessments in person with a study coordinator, or [3] the patient will take a paper copy home, complete it, and return it at either the next visit, via mail, or scan and email.

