### Sample size

#### Aim 1: Implementation outcome (patient level)

The RCT is powered for the aim 1 outcome, ENABLE program uptake, defined as the proportion of patients who complete the ENABLE program. In determining the targeted sample size, we made the following assumptions: [1] an intra-class correlation coefficient (ICC) value of 0.05, [2] alpha of 1% (*α* = 0.01) and 80% power, [3] 20% enrolled patients for whom completion of ENABLE cannot be assessed due to death or becoming too ill to continue with participation, and [4] a proportion of patients completing ENABLE of 0.52 in prior studies. With 24 practice clusters per group and a minimum of 12 patients per practice cluster (down from 15 after 20% unable to assess completion), for a total of 288 patients per group, the detectable difference in ENABLE program uptake is 0.18 (OR = 2.06; RR = 1.33), a medium effect size.

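### Exploratory aim 2 states its uptake hypothesis for practices but tests it through ENABLE sessions, apparently each patient's own, so the slope is open to confounding by decline after baseline

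*Protocol article*

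**What the plan says.** Under Study aims and hypotheses, the purpose of exploratory aim 2 is to "Determine the relationship among ENABLE program uptake, overall ENABLE program implementation" and patients' QOL and mood. Its hypothesis concerns practices: "Practice clusters with better ENABLE program uptake and overall ENABLE implementation (regardless of implementation group) will demonstrate a higher degree of improved patient outcomes". The Primary aim defines uptake as "the proportion of patients who complete the ENABLE program (i.e., have a palliative care assessment and complete the six ENABLE sessions".

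The analysis section for exploratory aim 2 plans two models:

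- Uptake: "The association between ENABLE sessions and change in patient outcomes will be examined with linear mixed models". The adjustment is described as follows: "Adjusting covariates will include patient characteristics that may influence participation in sessions (e.g., sex, illness acuity, age".
- Implementation: "Linear mixed models will also be used to examine the association between GOI scores and patient outcomes". The GOI is scored once per practice cluster at each assessment.

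On timing, "Patient assessments will be completed at baseline, 12, and 24 weeks". The Aim 1 analysis counts a patient as a completer only if the assessment and all sessions are done before the 12-week assessments. The Aim 1 sample size section allows for "20% enrolled patients for whom completion of ENABLE cannot be assessed due to death or becoming too ill to continue with participation".

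**The concern.** The proportion of a practice's patients who complete ENABLE is never named as a predictor of patient outcomes. The uptake half of the hypothesis is approached through sessions instead, and the covariates listed are those that would explain an individual patient's participation. A slope on a patient's own sessions answers a different question: whether, largely within practices, patients who had more sessions fared better than patients who had fewer.

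That comparison is vulnerable in this population. These patients have recently diagnosed advanced cancer, sessions run inside the interval over which change is measured, and a patient who deteriorates may both miss sessions and report worse QOL and mood. The slope can then be positive when sessions do nothing. The end of Background and rationale expects greater uptake to lead to better outcomes, so a positive slope would readily be taken as support for that link.

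**Working it through.** **Level of hypothesis and analysis**

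| Half of the hypothesis | Level stated | Predictor planned | Level of predictor |
|---|---|---|---|
| Uptake | Practice cluster | ENABLE sessions | Not stated; patient level implied by the covariates |
| Overall implementation | Practice cluster | GOI score | Practice cluster |

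Only the uptake half is mismatched.

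**Inputs.** The protocol gives no power or effect size for this aim, so there is no figure to reproduce. From the sample size section: 48 clusters, 12 assessable patients each, and ICC 0.05 (stated there for uptake, borrowed here for the outcome). Everything else is assumed:

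- Decline D has SD 1. Baseline acuity has correlation ρ with D.
- Latent participation = 1 + practice effect (SD 0.6) − bD + noise (SD 1). Sessions = 4 + 1.5 × latent, rounded and held within 0 to 6.
- Outcome change = −bD + practice effect (variance 0.05) + noise (variance 0.95). The true session effect is zero.

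**Expected false slope.** Ignoring the 0-to-6 limits, the acuity-adjusted patient-level slope per session is

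b²(1 − ρ²) / {1.5 × [0.36 + 1 + b²(1 − ρ²)]}

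For b = 0.4:

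- ρ = 0: 0.16 / (1.5 × 1.52) = 0.070
- ρ = 0.5: 0.12 / (1.5 × 1.48) = 0.054
- ρ = 0.8: 0.0576 / (1.5 × 1.4176) = 0.027
- ρ = 1: 0

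Adjustment removes the share ρ² of the numerator, that is, the part of the decline that acuity predicts.

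**Simulation.** There were 300 trials per row, tested at nominal 5%. The patient-level model is least squares with practice-robust standard errors, standing in for the mixed model. The comparator regresses practice-mean change on practice-mean sessions, without acuity.

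| b | ρ | Patient slope, acuity-adjusted | Rejects | Practice-mean slope | Rejects |
|---|---|---|---|---|---|
| 0.2 | 0 | 0.024 | 12% | 0.003 | 5% |
| 0.2 | 0.5 | 0.018 | 12% | 0.010 | 6% |
| 0.2 | 0.8 | 0.010 | 8% | 0.008 | 3% |
| 0.2 | 1 | 0.001 | 7% | 0.009 | 4% |
| 0.4 | 0 | 0.092 | 71% | 0.027 | 6% |
| 0.4 | 0.5 | 0.069 | 47% | 0.029 | 7% |
| 0.4 | 0.8 | 0.034 | 12% | 0.030 | 7% |
| 0.4 | 1 | −0.004 | 8% | 0.024 | 4% |

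With no shared decline (b = 0), the patient-level model rejects in 5% to 7%. Without the acuity term it rejects in 11% to 14% (b = 0.2) and 66% to 74% (b = 0.4). The simulated slopes exceed the formula because the ceiling at six sessions compresses the exposure. Simulation error near 5% is √(0.05 × 0.95 / 300) = 1.3 percentage points, so 7% or 8% is not clearly above nominal.

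Other assumed strengths, with ρ = 0.5, gave acuity-adjusted patient-level rejection of 13% to 17% (weaker) and 86% to 99% (stronger), against 5% to 15% for practice means.

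**Why practice means are less biased, but not unbiased.** For b = 0.4, again ignoring the limits, the practice-mean slope is (0.16/12) / {1.5 × [0.36 + 1.16/12]} = 0.0133 / 0.685 = 0.019. If practices did not differ in participation (0.36 replaced by 0), it would be 0.0133 / (1.5 × 0.0967) = 0.092, the same as the within-practice slope 0.16 / (1.5 × 1.16) = 0.092. The gain therefore depends on real differences between practices.

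**The case against.** The strongest reply has four parts.

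- **The plan already adjusts for illness acuity, and its covariate list is open-ended.** This stands in part. Adjustment helps, and if acuity tracked later decline almost perfectly it would be enough. A baseline value cannot capture decline that it does not predict, and a value taken at 12 weeks would follow the sessions.
- **The GOI model is at practice level.** This stands. A reader might infer that the whole aim is analysed at the wrong level, and the analysis section does not support that. The GOI model does not, however, supply a test of uptake.
- **The text does not say that sessions are counted per patient, and an article leaves detail to the full protocol.** Patient level is an inference, though the covariates make it the natural one. The point rests on what the article states: a hypothesis about practice uptake, and an analysis that names sessions.
- **The aim is exploratory and worded as association.** This limits the severity. It does not make the model match the hypothesis.

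The supplementary Aim 1 comparisons of illness-related non-completion and of sessions completed are made between arms, so they do not address confounding inside this model. Nor does the 20% allowance measure the confounding: patients who die have no later outcome. It shows only that the protocol expects illness to stop participation.

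**Conclusion.** The point holds as a mismatch of level for the uptake half of exploratory aim 2, with a resulting risk of confounding by decline after baseline. The direction is towards a false benefit of sessions. The size is unknown: simulated false-positive rates for the acuity-adjusted patient-level model run from near nominal to very high, and the strength of confounding, its correlation with acuity and the spread between practices are all assumptions.

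A reader might infer that the planned model will produce a false benefit, or that a positive result is almost certain. The documents do not support this. They give no measure of how strongly decline affects sessions or outcomes, the planned model includes acuity, and under weak shared decline the result would usually be null. Because the aim is exploratory, this is a desirable improvement and does not threaten the trial's main conclusions.

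**What to change.** Reword the uptake analysis for exploratory aim 2:

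- Make practice-level uptake (the proportion completing, or practice mean sessions) the predictor for the hypothesis. Enter the patient's deviation from the practice mean as a separate term in the same linear mixed model. A leave-one-out practice mean adds nothing once the deviation is in the model.
- Adjust for the baseline value of the outcome and for illness acuity measured at baseline.
- Draw the uptake conclusion from the practice-level coefficient. Report the within-practice session slope as an association open to reverse causation.
- Keep the GOI model as the analysis of the implementation half.

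This changes analysis wording only and uses data already to be collected. The cost is lower precision, because the exposure varies over 48 practices. The practice-level estimate is less biased, not bias-free, and keeps more bias if practices differ little in uptake.

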## Discussion

The relative strengths of learning collaboratives compared to other implementation strategies are poorly understood [16, 17]. This study will provide a direct comparison between the VLC and TA strategies to determine if VLC is a superior method to facilitate implementation of the evidence-based ENABLE program in community-based oncology practices. Finding successful strategies to implement models of early palliative care in cancer is imperative given national guidelines that have highlighted this priority [70].

Most published studies on VLCs are descriptive and have not definitively tested its effectiveness to enhance adoption and implementation [16, 71–82]. There are also few randomized-clinical trials that evaluate traditional in-person learning collaboratives [14, 15, 21, 22] or compare their effectiveness to other implementation approaches [16, 17, 71, 83]. For example, learning collaboratives have been shown to outperform financial incentives or toolkits, but only on some process or secondary outcomes [16, 17]. This study will contribute to the fields of implementation science and palliative care as we will learn about the implementation effectiveness of VLC and TA while delivering an evidence-based practice. While we hypothesize the VLC will outperform TA due to the shared wisdom generated by the group, the VLC strategy has greater demands for sites and facilitators (and possibly costs) and has less opportinuity for individual attention than TA. As such, it is important to assess the added value of each strategy in order to know how to better spread and sustain EPC. Therefore, this study will inform efforts to more widely disseminate ENABLE, while simultaneously advancing implementation science methods and approaches that can be used for other evidence-based practices.

Like most research, we have encountered challenges during the study start-up period. First, the COVID-19 pandemic significantly impacted the ability for NCORP practices to conduct research and resulted in a need to rely on telehealth. Although most ENABLE activities were already offered via telephone, we modified the protocol so that all study procedures can now be conducted remotely, including the consent process and the comprehensive palliative care assessment. During this time, NCORP practices also expressed concern about the time required to complete the Nurse Coach training. To reduce training burden, the length of the web-based ENABLE Nurse Coach training was reduced from 25 h to approximately 19 h. We anticipate the reduced number of training hours may be beneficial beyond the study given our goal to make the ENABLE training more broadly scalable to nurses and advanced practice providers interested in implementing this EPC program. We also amended the originally required cohort size (*n* = 16) and will permit cohorts of 8–20 practice clusters (4–10 per study arm). To account for this in analyses, we will assess for confounding by cohort. Lastly, although each practice cluster will be expected to deliver ENABLE to 15–27 patients, we recognize that may not happen. To account for this, we will include an option to recruit additional practice clusters (up to 20% of 48 which is 58 practices) and additional cohorts. Despite these challenges, we anticipate the first cohort will launch in the first half of 2021.

There are several anticipated lessons learned from this study. First, to the best of our knowledge, this is the first large-scale study measuring the implementation of early palliative care in community-based oncology practices. To measure implementation, we developed and refined palliative care implementation measures and anticipate that lessons learned will be used to improve these measures. Second, this study not only seeks to identify the superior implementation strategy (VLC or TA), but also to examine the key components of each strategy. To do so, we have developed measures of participation, engagement, and fidelity that have not been applied in other published literature. Lessons learned will inform refinement of the measures and advance the field.

### Strengths and limitations

There are several strengths to this study. First, this study will evaluate both the uptake of an evidence-based EPC intervention and organizational factors associated with improving delivery of EPC in community based care. Second is the collaboration with the URCC NCORP. Conducting this work outside a consortium would be difficult, particularly with respect to recruiting practice clusters. Third, this study provides a solution to the limited palliative care workforce by implementing this program as a generalist palliative care model [84]. As part of study activities, Nurse Coaches will be trained on how to deliver the ENABLE EPC program, thereby increasing practice capacity to offer palliative care services [7, 8, 85]. A final, yet unanticipated strength to this study is the opportunity to implement the effective ENABLE EPC telehealth model in community oncology clinics during COVID-19 when telehealth services are particularly important.

While this study will contribute to implementation science methods and approaches, there are limitations. Patients and caregivers will not know which study arm their practice cluster is assigned. However, practice clusters will not be blinded to study aims and hypotheses as sharing those are essential to study recruitment and consent procedures. Similarly, blinding the TA and VLC facilitators and the assessors (e.g., ENABLE GOI interviewer) to the group assignment is not feasible. However, it is feasible to limit their knowledge of specific activities in each study arm to minimize bias. Contamination between practice cluster cohorts is another potential limitation. Since all practice clusters will be affiliated with URCC NCORP, enrolled practice clusters may discuss their study involvement with practices that register for a future cohort. To minimize potential contamination between cohorts, we will instruct second and third cohorts to reach out to the TA or VLC members (depending on randomization assignment) as opposed to outside practices for advice.

## Conclusion

The results from this study will be twofold: [1] we will learn about the implementation of an early palliative care intervention among community oncology practices, and [2] we will learn about the effectiveness of the VLC as compared to TA to facilitate such implementation. In addition, lessons learned will advance the field of implementation science through further refinement of palliative care implementation measures and of the VLC implementation strategy.

## Data Availability

The investigators will provide access to data according to NIH and University of Rochester NCI Community Oncology Research Program policies.

## Abbreviations

ACS: American Cancer Society
CCDR: Cancer Care Delivery Research
CCM: Chronic Care Model
CIC: Chronic Illness Care
CIRB: Central Institutional Review Board
CONSORT: Consolidated standards of reporting trials
CYC: Charting Your Course
DSMC: Data Safety Monitoring Committee
EBP: Evidence-based practice
ENABLE: Educate, Nurture, Advise, Before Life Ends
EPC: Early Palliative Care
ERIC: Expert Recommendations for Implementing Change
FACT-G: Functional Assessment of Cancer Therapy–General
FACIT-PAL: Functional Assessment of Chronic Illness-Palliative Care
GOI: General Organizational Index
HADS: Hospital Anxiety and Depression Scale
ICC: Intra-class Correlation Coefficient
LC: Learning Collaborative
BMCB: Montgomery Borgatta Caregiver Burden Scale
MDASI: MD Anderson Symptom Inventory
NCI: National Cancer Institute
NCORP: NCI Community Oncology Research program
PI: Principal investigator
PROMIS: Patient Reported Outcome Measurement Information System
QOL: Quality of life
RCT: Randomized controlled trial
RE-AIM: Reach, Effectiveness, Adoption, Implementation, Maintenance Framework
REDCap: Research Electronic Data Capture
RUCA: Rural-Urban Commuting Area
TA: Technical Assistance
UAB: University of Alabama at Birmingham
UR: University of Rochester
URCC: University of Rochester Cancer Center
VLC: Virtual Learning Collaborative
